# The value of a new cardiac magnetic resonance imaging protocol in Myocardial Infarction with Non-obstructive Coronary Arteries (MINOCA) – a case-control study using historical controls from a previous study with similar inclusion criteria

**DOI:** 10.1186/s12872-017-0611-5

**Published:** 2017-07-24

**Keywords:** Myocardial infarction, Non-obstructive coronaries, Cardiac magnetic imaging

## Abstract

**Background:**

Myocardial Infarction with Non-Obstructive Coronary Arteries (MINOCA) is common with a prevalence of 6% of all patients fulfilling the diagnosis of myocardial infarction. MINOCA should be considered a working diagnosis. Cardiac Magnetic Resonance (CMR) imaging has recently been suggested to be of great value to determine the cause behind MINOCA. The objectives of this paper are to describe the rationale behind the second Stockholm Myocardial Infarction with Normal Coronaries (SMINC-2) study and to discuss the protocol for investigation of MINOCA patients in the light of the recently published position paper from the European Society of Cardiology.

**Methods:**

The SMINC-2 study is an open non-randomised study using historical controls for comparison. The primary aim is to prove that MINOCA patients investigated with the latest CMR imaging technique can achieve a diagnosis in 70% of all cases entirely by imaging. By including 150 patients we will have >80% chance to prove that the diagnostic accuracy can be improved by 20 absolute % with a *p*-value of less than 0.05 when compared with CMR imaging in the SMINC-1 study. Furthermore, in addition to invasive coronary angiography, coronary arteries are evaluated by computed tomography angiography to investigate coronary causes and questionnaires are used to describe Quality-of-Life (QoL). By January 1st 2017, 75 patients have been included.

**Discussion:**

Whether CMR imaging can provide a diagnosis to an adequate proportion of MINOCA patients is unknown. Well-defined inclusion and exclusion criteria will be used to compare a MINOCA cohort from the population with an appropriate control group. Positive results are likely to influence future guidelines of the management of MINOCA. Furthermore, the study will give mechanistic insights into MINOCA in particular in patients with “true” myocardial infarction and describe QoL in this vulnerable group of patients.

**Trial registration:**

Clinical Trials NCT02318498.

## Background

Myocardial Infarction with Non-Obstructive Coronary Arteries (MINOCA) is common with a prevalence of 6% of all patients fulfilling the diagnosis of myocardial infarction [1]. A value of Cardiac Magnetic Resonance (CMR) imaging in MINOCA has recently been suggested. A meta-analysis of five CMR studies of MINOCA showed that one third of the patients had myocarditis and 20% had a “true” myocardial infarction [2]. Today, there are no guidelines on how to investigate and treat MINOCA, however a position paper on MINOCA was recently published by the European Society of Cardiology (ESC) working group on cardiovascular pharmacotherapy [3]. Most importantly, it stated that MINOCA should be considered a “working diagnosis” similar to heart failure. Coronary and non-coronary cardiac mechanisms should be investigated and non-cardiac reasons considered. Great emphasis was placed on CMR imaging in the investigation of MINOCA. CMR imaging was recommended in all MINOCA patients without a clear cause.

The Stockholm Myocardial Infarction with Normal Coronaries (SMINC) study was a study with the primary aim to investigate the role of endothelial function in MINOCA [4]. The results showed that endothelial function and common carotid intima-media thickness were normal when compared to controls. Furthermore, the risk factor profile resembled Coronary Heart Disease (CHD) controls with the exception for a non-atherogenic lipid profile. In the SMINC study, patients with myocarditis were excluded by CMR imaging. Other exclusion criteria were previous myocardial infarction, known cardiomyopathy, severely impaired renal function and Chronic Obstructive Pulmonary Disease (COPD) as well pulmonary embolism and type 2 myocardial infarction. The screening phase of the SMINC study of all patients investigated with CMR imaging showed that it was possible to assign a definitive diagnosis to 50% of the patients by performing CMR imaging and adding clinical information in particularly on the occurrence of Takotsubo stress CardioMyopathy (TCM) [5]. Major limitations of the CMR imaging in the SMINC study were that it was performed in median 12 days after the acute event and that the latest CMR imaging technique including T1 mapping to detect oedema was not performed. Furthermore, at that time there was no clear CMR imaging-based diagnosis for TCM. The second SMINC study (SMINC-2) is on-going with the *primary aim* to give 70% of the patients a definite diagnosis purely on the basis of the CMR imaging results. To be able to do this, the protocol states that CMR imaging should be performed 2-4 days after hospitalisation because of MINOCA and to include T1 mapping in addition to T2 oedema sequences. An overall *secondary aim* is to test a protocol on how to investigate MINOCA patients including further characterisation of these patients with emphasis on coronary imaging and stress. The objectives of this paper are to describe the rationale behind the SMINC-2 study and to discuss the protocol of investigation of MINOCA patients in the light of the recently published position paper [3].

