## Methods/design

The study design is an open non-randomised multi-center study using historical controls from the SMINC study for comparison. The primary aim is to prove that patients investigated with CMR imaging can achieve a definite diagnosis in 70% of all MINOCA cases entirely by imaging (Clinical Trials NCT02318498). By including 150 patients, we will have >80% chance to prove that the diagnostic accuracy can be improved by 20 absolute % with a *p*-value of less than 0.05 when compared with our previous sample [5]. By January 1st 2017, 75 patients have been included. The study is supported by grants provided by the Stockholm County Council (ALF project) and Swedish Research Council.

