## Discussion

The primary objective of the present paper is to describe the rationale behind the SMINC-2 study that has the aim to test if early CMR imaging using the latest technique can give more than 70% of all MINOCA patients a CMR imaging-based diagnosis. The main diagnoses that are possible to acquire are myocarditis, TCM and “true” myocardial infarction. Our previous meta-analysis of CMR imaging findings in MINOCA showed that one third of the patients had myocarditis and 20% had “true” myocardial infarction [2, 8]. These new studies shows that early CMR imaging (median 3, respectively 6 days) with conventional T2 oedema sequences gave the patients a definite diagnosis in 90%, respectively 87% of the cases. The reasons for these extraordinary figures are possibly due to study design where the results by Emrich and coworkers [7] are limited due to the retrospective design possibly including patients with already known or suspected diagnosis whereas in the prospective study by Pathik and co-workers [8] all-comers were included without exclusion criteria. Both studies were able to diagnose TCM by CMR imaging (10%, respectively 27%) thereby improving the diagnostic performance of CMR imaging. The results of the meta-analysis and the recent studies [2, 7, 8] support the idea that early CMR imaging with the latest CMR imaging technique can give the diagnosis in the vast majority of MINOCA patients thus being an important diagnostic tool as pointed out in the recent position paper by the ESC [3].

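### The implied 50% control rate counts CMR plus clinical information while the SMINC-2 endpoint is imaging alone, so the primary comparison is not like for like

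*Protocol article*

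**What the plan says.** The Background of the protocol article gives the source of the historical figure. In the screening phase of the SMINC study (SMINC-1 in the abstract), "it was possible to assign a definitive diagnosis to 50% of the patients by performing CMR imaging and adding clinical information", particularly about TCM. The same section indicates why clinical information was needed: "at that time there was no clear CMR imaging-based diagnosis for TCM".

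The SMINC-2 endpoint is defined differently. The Background states the primary aim as "to give 70% of the patients a definite diagnosis purely on the basis of the CMR imaging results", and Methods/design repeats that patients "can achieve a definite diagnosis in 70% of all MINOCA cases entirely by imaging".

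The sample-size sentence in Methods/design says that 150 patients give a better than 80% chance, at p below 0.05, of proving that "the diagnostic accuracy can be improved by 20 absolute" per cent. The comparator is the group's previous sample, with the same reference [5] that supports the 50%. The Methods paragraph of the abstract makes the same statement, but there the comparator reads "when compared with CMR imaging in the SMINC-1 study", with no mention of clinical information.

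No section gives the SMINC rate on imaging alone or the number of SMINC controls, or says that SMINC cases will be scored again on imaging alone.

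**The concern.** The difference from the historical cohort is the trial's primary result, and the Conclusion expects a positive result to influence guidelines. That difference is meant to show what the newer, earlier CMR protocol adds. It can do so only if a diagnosis is counted in the same way in both cohorts.

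Here one side counts diagnoses made by imaging alone, and the other counts diagnoses made by imaging plus clinical information. The article also leaves unclear which SMINC figure will be used. The body points to the composite 50%, while the abstract's wording points to an imaging-only figure. The two would bias the comparison in different ways:

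- Against the composite, an imaging gain is understated and power for it is lost.
- Against an imaging-only figure, a diagnosis for which SMINC had no clear CMR definition (TCM) is set against a cohort where it is a CMR category.

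**Working it through.** **Inputs from the article.** Target 70% (Background, Methods/design); absolute improvement 20 points; 150 SMINC-2 patients; p < 0.05; power above 80%. Implied control rate: 70 − 20 = 50%.

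**Assumed, because not stated.** A two-sided test, the number of controls, and the points *c* of the 50% that came only from clinical information.

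**Method.** Normal approximation for two proportions with pooled variance under the null:

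power = Φ{ [ |p₂ − p₁| − 1.96·√(p̄(1 − p̄)(1/n₁ + 1/n₂)) ] / √(p₁(1 − p₁)/n₁ + p₂(1 − p₂)/n₂) }

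**1. The plan's own figure.** For 50% v 70% with 150 v 150, p̄ = 0.60. The pooled standard error is √(0.24 × 2/150) = 0.0566 and the unpooled one is √((0.25 + 0.21)/150) = 0.0554. Power = Φ[(0.200 − 1.96 × 0.0566)/0.0554] = Φ(1.61) = 95%. With 150 SMINC-2 patients and other control numbers, power is 72% (50 controls), 83% (75), 89% (100) and 97% (200). It passes 80% from 66 controls. The stated figure is therefore consistent with 50% v 70% for any control group of 66 or more, and the arithmetic is not at fault.

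**2. What the mismatch does to the estimate.** Let the SMINC imaging-only rate be 50 − *c* and let the true imaging gain be *g* points. The SMINC-2 rate is then 50 − *c* + *g*. Against the composite 50%, the expected difference is *g* − *c*, so the imaging gain is understated by exactly *c*.

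**3. What it does to power.** Take a true imaging gain of 20 points, still tested against the composite 50%. For *c* = 5, SMINC-2 is at 65%, and with 150 v 150 power = Φ[(0.150 − 1.96 × 0.0571)/0.0564] = Φ(0.68) = 75%. For *c* = 10, SMINC-2 is at 60%, and power = Φ[(0.100 − 1.96 × 0.0574)/0.0572] = Φ(−0.22) = 41%.

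| *c* | SMINC imaging-only | SMINC-2 imaging-only | Power v composite 50%, with 100 / 150 / 200 controls | Power v matched imaging-only rate |
|---|---|---|---|---|
| 0 | 50% | 70% | 89 / 95 / 97% | 89 / 95 / 97% |
| 5 | 45% | 65% | 66 / 75 / 80% | 88 / 94 / 96% |
| 10 | 40% | 60% | 34 / 41 / 46% | 88 / 94 / 96% |
| 15 | 35% | 55% | 12 / 14 / 15% | 88 / 94 / 96% |

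The matched comparison keeps its power throughout. The loss comes only from the change of definition.

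**4. The other control.** If the imaging-only rate 50 − *c* were used and SMINC-2 still reached 70%, the contrast would be 20 + *c* points. With 150 controls, power would be 99% at a control rate of 45% and above 99% at 40%. To the extent that *c* is TCM, some of that larger contrast reflects TCM becoming a CMR category.

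**The case against.** The strongest reply is that the mismatch is disclosed in the Background and is conservative. The composite rate is at or above the imaging-only rate, so a significant result against 50% would still show superiority. If SMINC-2 truly reaches 70% by imaging, the planned power is intact. All of this stands, and it is why the point does not threaten the validity of a positive finding. It does not make the difference a measure of the gain in CMR yield, which is how the abstract presents it.

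A second reply is that detecting TCM by CMR is part of what is being tested. This stands in part. The Background lists the missing TCM definition beside late scanning (median 12 days) and the absence of T1 mapping. The Investigations section bases acute TCM on T1-mapping oedema and/or transient wall-motion abnormality. Some of any TCM gain would be a real benefit of earlier scanning and T1 mapping.

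A reader might infer something stronger: that moving TCM from a clinical to an imaging diagnosis could by itself produce the planned 20 points. The article does not support this. The implied control already counts clinically assigned TCM, so reclassification with no other change gives 50% v 50%, a difference of zero. Inflation could arise only against an imaging-only control, and no section fixes such a rate. The TCM shares in the Discussion (10% and 27%) come from two other cohorts whose design and selection the article itself distinguishes from SMINC-2. They cannot be read as SMINC's share. Nor does the lack of a clear CMR definition show that SMINC scans could never suggest TCM.

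**Conclusion.** Wrong as written, and it should be fixed. The implied 50% is a composite of CMR and clinical information, the SMINC-2 endpoint is imaging alone, and the abstract misdescribes the comparator. As stated, the comparison is conservative. It understates the CMR gain by the unknown contribution of clinical information and, for a true 20-point imaging gain, lowers power to about 75% if that contribution was 5 points and 41% if it was 10.

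These figures are illustrations. They assume a two-sided 5% test, 150 controls, and clinical information that added diagnoses and removed none. The article gives neither the control number nor the imaging-only rate. It would be wrong to conclude that 150 patients are too few for 50% v 70%, or that the planned test has an inflated false-positive rate.

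**What to change.** 1. From existing SMINC records, tabulate how many patients were diagnosed by CMR alone and how many by CMR plus clinical information.
2. Name one definition, applied to both cohorts, as the primary comparison, and report the other as secondary. Make the choice before the cohorts are compared.
3. Add a line limited to myocarditis plus infarction, so that the part of the difference that does not depend on TCM can be seen.
4. Restate the control rate, the number of controls and the power for the chosen definition.
5. Correct the abstract so that the 50% is described as CMR plus clinical information.

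Reading the SMINC scans again under the SMINC-2 rules is not proposed. Those rules require T1-mapping oedema for infarction and myocarditis, and SMINC did not acquire T1 mapping.

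The cost is a little retabulation and some wording, plus a clinically supplemented diagnosis for SMINC-2 patients if that is not already recorded. No new patients are needed. The stated 20-point contrast, or the power, may change.

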## Methods/design

The study design is an open non-randomised multi-center study using historical controls from the SMINC study for comparison. The primary aim is to prove that patients investigated with CMR imaging can achieve a definite diagnosis in 70% of all MINOCA cases entirely by imaging (Clinical Trials NCT02318498). By including 150 patients, we will have >80% chance to prove that the diagnostic accuracy can be improved by 20 absolute % with a *p*-value of less than 0.05 when compared with our previous sample [5]. By January 1st 2017, 75 patients have been included. The study is supported by grants provided by the Stockholm County Council (ALF project) and Swedish Research Council.

### Inclusion criteria

Consecutive patients from the five major hospitals in Stockholm, 35-69 years old, fulfilling the existing diagnostic criteria of myocardial infarction [6] with angiographically normal coronary arteries will be included. Coronary angiography will be performed according to the individual laboratory including 4-5 projections of the left coronary artery and 2-3 projections of the right coronary artery. Patients with angiographically completely normal coronary angiography or with signs of diffuse coronary atherosclerosis with no lesion giving rise to a measurable stenosis of any percentage will be included. If doubt a Quantitative Coronary Analysis (QCA) should be performed on the projection showing the most narrow intrusion and the patient excluded if the results shows a stenosis of >20% that is the lowest limit of detection with QCA. All coronary angiograms should be evaluated by two experienced angiographers.

### Exclusion criteria

Patients without sinus rhythm on admission ECG, pulmonary embolism, COPD, previous myocardial infarction, known cardiomyopathy or severe renal impairment (serum creatinine above 150 umol/l) will be excluded.

Patients with a pacemaker and claustrophobia will be excluded due to interference with interpretation or possibility to perform CMR imaging.

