### Strength and limitations

The major strengths of SMINC-2 are the fairly high number of patients included from several hospitals being representative for a north European population and in comparison with several previous studies it is prospective and the first one with a control group. Limitations include the fairly strict age criteria and that it will not include patients with near significant coronary artery stenosis to be able to have the SMINC study as a control group. The reasons for the strict age criteria in the SMINC study were that it was unlikely that all patients would receive a coronary angiography if patients were below 35 and above 69 years of age. The reason for the lower age limit is that the likelihood is much higher for myocarditis than CHD and thus the diagnosis would be made without a coronary angiography. Regarding the upper age limit, many patients 70 years and older with suspected CHD were treated conservatively at the time of the start of the SMINC study 10 years ago. This together with the fairly strict inclusion and exclusion criteria may somewhat limit the representativity of the study.

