## Conclusion

Whether CMR imaging can provide a diagnosis to an adequate proportion of MINOCA patients is unknown. Well-defined inclusion and exclusion criteria will be used to compare a MINOCA cohort from the population with an appropriate control group. Positive results are likely to influence future guidelines of the management of MINOCA. Furthermore, the study will give mechanistic insights into MINOCA in particular in patients with “true” myocardial infarction and describe QoL in this vulnerable group of patients.

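### Type 2 infarction is a listed exclusion for the historical SMINC study but not for SMINC-2, so the two cohorts compared in the primary analysis may differ in case mix

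*Protocol article*

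**What the plan says.** The Methods/design section describes an open, non-randomised study with historical controls from SMINC. The aim is that patients "can achieve a definite diagnosis in 70% of all MINOCA cases entirely by imaging". The sample-size statement reads "By including 150 patients, we will have >80% chance to prove that the diagnostic accuracy can be improved by 20 absolute" per cent, with a p-"value of less than 0.05 when compared with our previous sample".

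The Background gives the exclusions of the first study: previous infarction, known cardiomyopathy, severely impaired renal function and COPD, "as well pulmonary embolism and type 2 myocardial infarction". Myocarditis was also excluded, but by the CMR scan itself. The comparator is that study's screening phase, meaning everyone scanned, in whom half received a diagnosis.

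For SMINC-2, the Exclusion criteria section lists "Patients without sinus rhythm on admission ECG, pulmonary embolism, COPD, previous myocardial infarction, known cardiomyopathy or severe renal impairment", and adds "Patients with a pacemaker and claustrophobia will be excluded" because these interfere with CMR. The Inclusion criteria section requires that the existing infarction criteria be met, with angiographically normal coronary arteries and age 35 to 69. It says nothing about infarction type.

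Under Strength and limitations, the article explains that the age range and stenosis limit were kept so that SMINC could serve as control. The Conclusion says the criteria will be used to "compare a MINOCA cohort from the population with an appropriate control group".

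**The concern.** With a historical control, the only protection against confounding in the design itself is that the same kinds of patients enter both cohorts. The endpoint is the proportion given a diagnosis of infarction, myocarditis or Takotsubo cardiomyopathy, and that proportion depends on who is let in. The Discussion accepts this when it attributes the 87% and 90% yields of two other CMR studies partly to how their patients were selected.

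The article gives up some representativeness in order to match SMINC on age and stenosis. It then leaves one stated SMINC exclusion unmatched, without comment, and the limitations do not mention it. A site following the SMINC-2 list as printed would enrol patients whom the first study excluded. Any difference in yield caused by those patients would be credited to, or charged against, the new CMR protocol.

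**Working it through.** **1. The two lists side by side**

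| Criterion | SMINC (Background) | SMINC-2 (Exclusion criteria) |
|---|---|---|
| Previous infarction | yes | yes |
| Known cardiomyopathy | yes | yes |
| Severe renal impairment | yes | yes |
| COPD | yes | yes |
| Pulmonary embolism | yes | yes |
| Type 2 infarction | yes | **not listed** |
| No sinus rhythm on admission | **not listed** | yes |
| Pacemaker, claustrophobia | not listed | yes (CMR feasibility) |
| Myocarditis | by CMR, so still in the scanned sample | not excluded |

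Five of the six non-CMR exclusions in the SMINC list are repeated. One, type 2 infarction, is not.

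**2. The plan's own power figure**

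Inputs: 150 new patients, control rate 0.50, target rate 0.70, significance level 0.05 (taken as two-sided; the article does not say). The control size m is not given. The test is the pooled two-proportion z-test:

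power = Φ{[(p2 − p1) − 1.96·SE0] / SE1}, with SE0 = √[p̄(1 − p̄)(1/m + 1/150)] and SE1 = √[p1(1 − p1)/m + p2(1 − p2)/150].

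For m = 75:
- p̄ = (37.5 + 105)/225 = 0.633, SE0 = 0.0682, SE1 = √(0.25/75 + 0.21/150) = 0.0688.
- (0.20 − 1.96 × 0.0682)/0.0688 = 0.97, so power is 83%.

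For m = 100 and 150, power is 89% and 95%. The stated figure of more than 80% is reached once m is at least 66. It is attainable, but cannot be confirmed without m.

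**3. Illustration with type 2 infarctions in SMINC-2 only**

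Assumptions, not from the article: 10% of SMINC-2 patients are type 2 infarctions, and 25% of those get a CMR diagnosis. The observed rate becomes 0.9 × 0.70 + 0.1 × 0.25 = 0.655.

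For m = 75:
- p̄ = (37.5 + 98.25)/225 = 0.603, SE0 = 0.0692, SE1 = √(0.25/75 + 0.655 × 0.345/150) = 0.0696.
- (0.155 − 1.96 × 0.0692)/0.0696 = 0.28, so power is 61%.

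| Control n (assumed) | Power at 70% | Power at 65.5% |
|---|---|---|
| 75 | 83% | 61% |
| 100 | 89% | 69% |
| 150 | 95% | 79% |

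These come from exact enumeration of the same test. The normal formula agrees to the nearest per cent, except 78% rather than 79% in the last cell.

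**4. The direction is open**

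Suppose the new protocol brings no gain, so that its true rate is 50% in comparable patients.
- With 10% type 2 infarctions at 25% yield, the observed rate is 0.9 × 0.50 + 0.1 × 0.25 = 0.475. The chance of a significant result favouring SMINC-2 is about 1%, below the nominal 2.5%.
- With 10% at 100% yield, the observed rate is 0.9 × 0.50 + 0.1 × 1.00 = 0.55. That chance becomes 11% / 12% / 15% for m = 75 / 100 / 150.

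The sign depends on whether the extra patients are diagnosed more or less often than the rest.

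**The case against.** The strongest reply is that the mismatch has not been shown in the actual comparator. The control is SMINC's CMR screening sample. Myocarditis was a SMINC exclusion yet remains in that sample, because the scan was what identified it. Type 2 infarctions could likewise still be there, depending on whether they were removed before or after CMR. The article does not say. This stands as a reason for asking, and it is why the control sample must be flagged too. It does not settle the matter, because nothing in the article shows that the two cohorts were treated alike.

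Several stronger readings are tempting and are not supported:

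- *SMINC-2 abandons the SMINC exclusions.* Only one is missing. The title claims similar inclusion criteria, and most criteria do match.
- *The added exclusions shift the case mix.* Pacemaker and claustrophobia concern the ability to scan, and all controls were scanned, so these carry little weight. The Background is a short summary, so its silence on sinus rhythm does not prove that the criterion was not used.
- *The comparison is unadjusted, or unscanned patients are miscounted.* The article fixes neither the test, nor adjustment, nor the denominator rule. These may be in a document not shown.
- *The era gap changed the infarction definition.* The remark "at the time of the start of the SMINC study 10 years ago" explains the upper age limit. It does not show that different infarction criteria were used.
- *The mismatch inflates false positives.* That needs extra patients with a higher yield than the rest. With low-yield type 2 infarctions, the effect is a loss of power.

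**Conclusion.** The point holds in a limited form. As printed, the eligibility criteria for SMINC and SMINC-2 disagree on type 2 infarction, and possibly on admission rhythm. The primary inference rests on a historical comparison that the article defends by pointing to matched criteria, so the disagreement should be resolved before analysis.

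Neither the direction nor the size of any bias can be determined from the article, because the share of type 2 infarctions, their CMR yield and the control sample size are all missing. The illustrated fall from 70% to 65.5%, with 16 to 22 points of power lost (95% to 79%, up to 83% to 61%), rests on an assumed 10% share, an assumed 25% yield, an assumed control n of 75 to 150, and no type 2 infarctions among the controls. It shows that a modest mismatch could matter; it does not estimate what will happen. The omission may be purely editorial, in which case a correction to the text settles the type 2 question.

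**What to change.** 1. Reconcile the Background and the Exclusion criteria on type 2 infarction: state whether it is excluded from SMINC-2, and whether it was removed from the SMINC CMR screening sample before or after the scan.
2. Flag type 2 infarction and admission rhythm in both datasets, including the SMINC screening sample that serves as control.
3. Run the primary comparison in patients who meet one common set of criteria.
4. Report beside it the comparison in all included patients and an estimate adjusted for age and sex from the SMINC patient-level data.

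The cost is text, chart review and access to the SMINC records; no new patients are needed. Only 75 of the 150 had been included by 1 January 2017, so the rule could be set well before the end of enrolment. The downside is that a few patients leave the primary comparison and precision falls slightly. Under the illustration above, removing the 15 type 2 infarctions (10% of 150) leaves 135 patients at a rate of 70%. The same test then has power of 82% / 88% / 93% for a control n of 75 / 100 / 150. That is one to two points below the full-sample figures, and well above the 61% / 69% / 79% with the mismatch left in. If controls also drop out on the common criteria, the loss is somewhat larger. Should the SMINC records lack type 2 status or admission rhythm, that should be stated as a limitation of the comparison.
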